### Sample size calculation

Sample size was estimated using G*Power 3.1.9.2. With a small effect size of 0.05, 0.05 type I error, 0.95 power of study and 10 predictive factors to be included into the model, the study will need to recruit 262 subjects. The final estimated sample size will be 420 cases after considering 20% attrition rate at each time point [(262 × 0.2) × 3 + 262] up to 2 years. Recruitment will be continued through the entire period to maximize statistical power.

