#### Prognostic factors that influence the rehabilitation outcomes

Linear regression modelling will be used to investigate the factors that influence the knee function of the patients. Simple linear regression will be used to explore the variables which significantly predict the outcome, and stepwise variable selection method will be used to build the multivariable models. Multicollinearity and interaction terms of the final model will be checked, and heteroscedasticity. The model fit will be checked and assessed using Hosmer-Leme show goodness of fit test. In secondary analysis, mixed effect generalized linear models will be used to explore the changes in outcomes across time as well as the factors predicting the outcome of interest. Mediation analyses will also be conducted to explore the potential mediating psychosocial factors between predictors with clinical outcomes. Structural equation modelling (SEM) cross lagged analysis, an analytical strategy used to describe reciprocal relationships or directional influences, between variables over time, will be used to estimate the directional effects of various psychosocial factors at different time points. Statistical significance will be denoted as *p* < 0.05.

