Results from this study can be used in several ways. Firstly, it can help raise awareness among clinicians who manage patients with knee OA to identify high risk knee OA subpopulations that will likely experience poor outcomes based on pre-existing factors. This would allow them to address these factors and potentially formulate targeted approaches to address these psychosocial factors to optimize non-surgical treatment care, maximize functional outcomes and reducing/delaying the need for expensive surgery. Secondly, the results will inform the development of holistic biopsychosocial integrated multidisciplinary care models that specifically targets high-risk population groups to intervene on prognostic psychosocial factors to optimize outcomes. Results can also be used to augment existing clinical practice guidelines and promote cross-disciplinary training and collaboration to further support integrated care models.

For this study, recruitment will primarily be centred around the tertiary hospitals as patients presenting to the hospital are more likely to be experiencing more symptomatic and debilitating knee OA with the corresponding associated psychosocial factors. This will allow for relationships between psychosocial factors and outcomes to be more clearly established through a well-defined hospital-based cohort. In the next phase upon completion of this study, there are plans for subsequent phases of the cohort study to be expanded further downstream to primary care and the community and to explore other psychosocial factors that emerge over time as part of the larger effort to develop a comprehensive biopsychosocial understanding of knee OA.

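### Stepwise selection tests each psychosocial factor conditional on its possible mediators, so the selected set cannot be read as the factors that influence knee function or as intervention targets

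*Protocol article*

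**What the plan says.** The section on prognostic factors in the statistical analysis plan states the purpose of the main analysis: "Linear regression modelling will be used to investigate the factors that influence the knee function of the patients". Simple linear regressions come first, to find variables that significantly predict the outcome. Stepwise selection then builds the multivariable models.

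The same section adds: "Mediation analyses will also be conducted to explore the potential mediating psychosocial factors between predictors with clinical outcomes". Cross-lagged structural equation modelling (SEM) follows, to estimate directional effects. The study aims make prognosis the primary aim, and mediation and direction a secondary aim.

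The Discussion hopes that the results will help care models to "intervene on prognostic psychosocial factors to optimize outcomes", and speaks of psychosocial parameters that may be modifiable.

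The sample size section gives the planning values: "With a small effect size of 0.05, 0.05 type I error, 0.95 power of study", with "10 predictive factors to be included into the model", from which "the study will need to recruit 262 subjects".

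**The concern.** In a stepwise model each factor is kept or removed on its coefficient given the other factors present. If factor X acts on KOOS-12 partly through factor M, and M is also a candidate, the coefficient of X estimates only the part of its effect that does not pass through M. The larger the mediated share, the smaller that coefficient and the likelier X is to be removed.

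The plan expects such pathways, yet nothing in the described analysis keeps the total association of X in view with adjustment. The simple regressions show it, but without age, radiographic grade or comorbidity.

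For a prediction rule this costs little. What is at stake is the interpretation. A factor missing from the selected set could be taken as unimportant, and a coefficient in that set could be taken as what would happen if the factor were changed. Neither follows from a model that may have adjusted for mediators.

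**Working it through.** **Inputs from the protocol article.** Effect size 0.05, type I error 0.05, power 0.95, 10 predictors and N = 262 (Sample size calculation); significance at p < 0.05 (Statistical analysis plan). The scale of the effect size and the sidedness of the test are not stated.

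**Reproducing 262.** Take 0.05 as Cohen's f² and test one coefficient, two-sided, in a model with 10 predictors:

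- df = N − 10 − 1 = 251
- noncentrality = √(f² × N) = √(0.05 × 262) = 3.62
- power from the noncentral t distribution = 0.9501

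So 262 is reproduced exactly. A one-sided test would need 218, and the overall F test of all 10 predictors would need 497. The design is therefore powered for one factor conditional on the other nine.

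**Assumptions not in the documents.** A standardised chain X → M → Y with one mediator. The total effect of X is set at f² = 0.05, so the standardised total effect is c = √(0.05/1.05) = 0.218. The correlation between X and M is a = 0.3 or 0.5. The mediated share m runs from 0 to 100%.

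**Formulas.**

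- Direct effect: c′ = c(1 − m)
- Mediator effect: b = m·c/a
- R² = c′² + b² + 2·c′·b·a
- Adjusted f² for X = c′²(1 − a²)/(1 − R²)

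**Worked case, m = 50%, a = 0.5.**

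- c′ = 0.109 and b = 0.218
- R² = 0.0119 + 0.0476 + 0.0238 = 0.083
- Adjusted f² = 0.0119 × 0.75/0.917 = 0.0097
- Power of the adjusted test at N = 262: 36%

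With a = 0.3 the adjusted f² is 0.0130 and the power 45%. At N = 420 the two powers are 52% and 65%. The test of the total effect has about 95% power at N = 262.

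**Simulation.** N = 262, 3,000 samples per setting, backward selection at p < 0.05 with X and M as candidates. The article does not state the direction of selection or the removal threshold. Each cell gives a = 0.3 / a = 0.5.

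| Share mediated | X significant alone | X retained | X significant alone but dropped |
|---|---|---|---|
| 0% | 95.1% / 94.8% | 94.9% / 93.2% | 0.6% / 2.3% |
| 25% | 94.5% / 94.5% | 73.7% / 71.6% | 20.8% / 22.8% |
| 50% | 95.0% / 94.0% | 44.7% / 37.0% | 50.3% / 57.0% |
| 75% | 94.9% / 94.1% | 16.4% / 13.7% | 78.5% / 80.7% |
| 100% | 94.9% / 94.4% | 4.6% / 5.1% | 91.6% / 91.4% |

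The last row is the extreme. The direct effect there is zero, so retention equals the test's own error rate. With a = 0.3 it also requires a very strong mediator (b = 0.727).

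**The case against.** **The primary aim is prognostic.** The article cites a prognostic research framework, and the section heading speaks of prognostic factors. Dropping a factor that adds nothing beyond a measured one is what a prediction model should do. This stands. The fault lies only in a causal reading of the selected set.

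**Mediation has its own analyses.** A direct effect near zero beside a non-zero indirect effect is what mediation means, so the two analyses need not contradict each other. This stands in part. The article does not say that factors removed by stepwise still enter the mediation or SEM analyses. Table 4 also measures social support, injustice, shame, religion and built environment only at baseline, so reciprocal paths over time cannot be estimated for them.

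**A reader might infer that all psychosocial factors are forced into one model, and that social support in particular will be lost.** The documents do not say so. Selection is stepwise, the text refers to models in the plural, and Table 2 assigns some scales to phase 1 and others to phase 2. No factor is named as upstream or as a mediator. The phases do not remove the problem, because social support, depression and anxiety, fear of movement and pain experience carry no phase mark and can be candidates together.

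**A reader might also infer that the plan declares the stepwise survivors to be intervention targets.** It does not. The Discussion speaks of the study's results as a whole, which include mediation and SEM. But it draws no line between the prediction model and the causal analyses, and the regression is itself introduced as a study of influence.

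**The planned effect size may be a partial effect.** Since 262 reproduces as a conditional test, f² = 0.05 can be read as already adjusted. Using it as the total effect is an assumption of the illustration, and the sample size calculation is not shown to be wrong.

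**One-factor models are confounded too.** If distress lowers perceived support rather than the reverse, the cross-sectional correlations are the same and support has no effect, yet a one-factor model would flag it. The Background itself describes pain and psychological symptoms as possibly reciprocal. This stands and limits the fix.

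**Causal orderings and adjustment sets belong in a full SAP.** Their absence from the article is not the point. The point rests on what the article states: conditional selection, expected mediators, and language of influence and intervention.

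**Conclusion.** The concern holds in a limited form. An upstream psychosocial factor may, not will, lose stepwise selection although its total association with KOOS-12 is real. With a total f² of 0.05, N = 262, one mediator and backward selection at 0.05, the proportion of samples in which a factor significant on its own is dropped runs from about 1–2% with no mediation to 91–92% with full mediation, passing 50–57% when half is mediated. The documents give no mediated share, so no single figure can be claimed.

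The stepwise model is fit for prediction. It does not show which factors influence function or what would change if one of them were modified. The unadjusted simple regressions and the later mediation and SEM analyses narrow the gap without closing it. The change is worth making because it is cheap; the point does not invalidate the design.

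**What to change.** 1. For every psychosocial factor, add a model containing that factor and the same fixed set of non-psychosocial baseline variables already collected, for example age, sex, Kellgren-Lawrence grade and Charlson index. Report each estimate with its interval whether or not stepwise selection keeps the factor.
2. State that all psychosocial factors are carried into the mediation and SEM analyses regardless of stepwise survival, as far as their measurement times allow.
3. Describe the stepwise model as a prediction model, and do not call its coefficients influences.
4. Do not declare causal targets from the one-factor models alone. They remain open to confounding by other psychosocial factors, and the causal order among those factors cannot be presumed.

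Cost: about nine further regressions per outcome (Table 2 lists nine psychosocial variables; pain acceptance, in Table 3, would be a tenth), some rewording and a longer results table. No new data are needed.

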#### Handling of missing data

The missing data percentage will be explored and addressed when appropriate. Logistic regression will be used to ascertain the missing data mechanism and the association between the missingness and baseline covariates. Where appropriate, multiple imputation with predictive mean matching (PMM) will be used to predict and impute the missing continuous data based on the observed baseline covariates at each follow-up. On the other hand, the imputation of binary outcomes will be done using the ‘miimputelogit’ package from STATA [57].

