#### Outcome measures timepoints

Upon baseline outcome measure taking, participants will be followed up at 4 months, 12 months, and annually after that. To reduce respondent fatigue and keep questionnaire burden to the minimum, psychosocial variables will be administered in two phases (Table 2) with a core set of outcome measures collected at all time points. In addition, certain psychosocial variables eg. built environment, that are not anticipated to change significantly over time will only be taken at baseline (Table 4).

**Table 4 Tab4:** Data collection at different time points

Measure	Baseline	4 month	12 month	24 month

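### Missing follow-up scores are to be imputed from baseline covariates, without the 4- and 12-month scores already collected; if such data feed the cross-lagged models, wave-to-wave paths are attenuated

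*Protocol article*

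**What the plan says.** Under Handling of missing data, the article says "Where appropriate, multiple imputation with predictive mean matching (PMM) will be used" to "impute the missing continuous data based on the observed baseline covariates at each follow-up". No earlier follow-up score is named as a predictor. Binary outcomes are to be imputed by a logistic routine, with no predictors given. The same section says: "Logistic regression will be used to ascertain the missing data mechanism and the association between the missingness and baseline covariates".

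Under Outcome measures timepoints, "participants will be followed up at 4 months, 12 months, and annually after that". Table 4 has knee function, depression and anxiety, pain experience, fear of movement, self-efficacy and pain acceptance at baseline, 4, 12 and 24 months. Injustice experience, social support, illness shame, religion and built environment are taken at baseline only.

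Under Prognostic factors that influence the rehabilitation outcomes, linear regression of knee function comes first. Mixed-effects models across time follow as secondary analysis, then mediation and "Structural equation modelling (SEM) cross lagged analysis, an analytical strategy used to describe reciprocal relationships or directional influences". The Sample size calculation assumes a "20% attrition rate at each time point".

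**The concern.** A participant seen at 4 and 12 months but lost at 24 months has two recent KOOS-12 scores, which are usually the best predictors of the missing one. The stated model passes over both. This has two consequences.

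First, each imputed value is independent of the interim scores given baseline. A cross-lagged model estimates exactly those visit-to-visit associations, so the imputation removes part of what the analysis is meant to measure. This follows from the method and needs no assumption about why people drop out.

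Second, if patients with worse interim scores are likelier to leave, conditioning on baseline alone does not correct for it. The missingness regression names baseline covariates only, so as described it would not look for this pattern. Nor can a regression on observed data ascertain the mechanism, because it cannot exclude data missing not at random.

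At stake is mainly the secondary aim on directional relationships, together with estimates of 24-month level and change.

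**Working it through.** **Share missing at 24 months.** The plan gives no figure for the imputation itself, so its sample-size figures set the scale. 262 reproduces as a two-sided test of one coefficient (f² = 0.05, alpha 0.05, 10 predictors; power 0.9501). The inflation is (262 × 0.2) × 3 + 262 = 419.2, given as 420.
- Additive loss, as in that formula: 420 − 157.2 = 262.8 remain; 157.2/420 = 37% missing.
- Compounding loss: 420 × 0.8³ = 215 remain; 49% missing.

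**Why the association shrinks.** With a fraction p observed at 24 months, drop-out completely at random and imputation from baseline only, the pooled 12-to-24-month correlation is roughly p × r(12,24) + (1 − p) × r, where r is the correlation carried through baseline alone.

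**First simulation** (420 subjects, four waves, about 56% observed at 24 months, predictive mean matching, 5 imputations, 300 replicates; assumed wave-to-wave correlation about 0.74; completely random drop-out):
- 12-to-24-month correlation: 0.74 falls to 0.56.
- Autoregressive path: 0.69 falls to 0.49, that is 1 − 0.49/0.69 = 29%.
- Psychosocial path given 12-month KOOS-12: 0.13 rises to 0.20.
- With earlier waves in the imputation model: 0.73–0.74, 0.68–0.69 and 0.12–0.13.

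Hand check: 0.56 × 0.74 + 0.44 × r = 0.56 gives r = 0.33, a plausible value. With 37% missing the same formula gives 0.63 × 0.74 + 0.37 × 0.33 = 0.59, so the loss is somewhat smaller but remains.

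**Second simulation** (420 subjects, four waves, about 20% monotone drop-out per wave, 5 donors, 10 imputations, 150–200 replicates; 44% to 49% missing at 24 months). The four sets of paths and the drop-out strength are assumptions. Path entries read: complete data → baseline-only → with earlier waves. The true 24-month mean is 0; its column reads baseline-only → with earlier waves.

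| True autoregressive; cross-lagged | Drop-out depends on | Autoregressive path | Cross-lagged path | 24-month mean (SD) |
|---|---|---|---|---|
| 0.60; −0.20 | nothing | 0.602 → 0.384 → 0.595 | −0.196 → −0.186 → −0.190 | −0.004 → −0.007 |
| 0.60; −0.20 | baseline | 0.599 → 0.399 → 0.591 | −0.201 → −0.188 → −0.195 | 0.011 → 0.011 |
| 0.60; −0.20 | previous visit | 0.605 → 0.371 → 0.585 | −0.196 → −0.188 → −0.193 | 0.115 → 0.019 |
| 0.40; −0.30 | baseline | 0.398 → 0.262 → 0.388 | −0.299 → −0.209 → −0.296 | 0.005 → −0.002 |
| 0.40; −0.30 | previous visit | 0.404 → 0.248 → 0.392 | −0.296 → −0.201 → −0.293 | 0.068 → 0.006 |
| 0.60; 0 | baseline | 0.603 → 0.360 → 0.597 | 0.000 → −0.058 → −0.002 | −0.003 → −0.006 |
| 0.60; 0 | previous visit | 0.599 → 0.327 → 0.586 | −0.001 → −0.055 → −0.003 | 0.094 → 0.016 |
| 0.50; −0.30 | baseline | 0.503 → 0.323 → 0.491 | −0.302 → −0.201 → −0.303 | 0.011 → 0.010 |
| 0.50; −0.30 | previous visit | 0.497 → 0.296 → 0.484 | −0.307 → −0.197 → −0.309 | 0.078 → 0.009 |

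- Autoregressive path: the smallest loss is 1 − 0.399/0.599 = 33%, the largest 1 − 0.327/0.599 = 45%.
- Cross-lagged path: about one third too small in two sets, hardly changed in one, and non-zero where the truth is zero in one. In the first simulation it was too large.
- 24-month mean: off by 0.07 to 0.12 SD when drop-out depends on the previous score, otherwise by about 0.01 SD at most.
- Regression of the 24-month score on the baseline predictor: −0.220 with complete data, −0.205 with baseline-only imputation, −0.211 with earlier waves (first set, drop-out depending on the previous visit).

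**The case against.** The strongest reply is that the text does not say imputed data enter the longitudinal models. Imputation is to be used at discretion; likelihood-based mixed models use every observed wave without it; and structural equation models can be fitted by full-information maximum likelihood. This stands, and it makes the consequence conditional. It does not repair the imputation model where that model is used.

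It can also be said that the word only is absent and that a journal article condenses a fuller plan. But the sentence names its predictors and applies them at every follow-up. That is a stated method, not a detail left open. Similarly, the missingness sentence lists the mechanism and the baseline associations as two things, so a restriction to baseline is a reading, though baseline covariates are all it names.

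Three stronger readings are tempting, and the documents do not support them:
- A reader might infer that all 24-month results are biased. The mean is biased only if drop-out depends on interim scores, and the article gives no drop-out mechanism. Regressions on baseline predictors, the first-listed analysis, barely move.
- A reader might infer that psychosocial effects will be overstated, by about 55% on the first simulation. That comes from one assumed set of paths; others gave attenuation, little change or a spurious effect.
- A reader might infer that half of the 24-month values will be imputed. The planned attrition gives 37% to 49% missing, and imputation is discretionary.

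Five of the psychosocial measures are taken at baseline only and cannot be lagged constructs at later visits, so cross-lagged harm is confined to the repeated ones. The number of imputations and a sensitivity analysis for data missing not at random are ordinary analysis-plan content, and no finding is made of their absence.

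**Conclusion.** The point holds in conditional form. The stated imputation model leaves out interim scores that the study collects and does not match the longitudinal analyses it may serve. If imputed data are used there, autoregressive paths are attenuated under every drop-out mechanism tried, completely random loss included, by roughly 30% to 45%. Cross-lagged paths are generally distorted, with no predictable direction. Bias of 0.07 to 0.12 SD in the 24-month mean, and hence in change, requires drop-out that depends on interim scores.

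The sizes rest on assumed paths, assumed drop-out strength and 44% to 49% missing; with 37% missing they would be somewhat smaller. Because the harm falls mainly on the secondary longitudinal analyses, this should be corrected before analysis but is not a critical defect.

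**What to change.** Reword the imputation sentence so that the model, for continuous and binary data alike, includes all available waves of KOOS-12 and the repeated psychosocial scores plus the other analysis variables. Chained equations with predictive mean matching and logit steps keep the methods already chosen. Alternatively, state that the mixed and structural equation models will use full-information likelihood on all observed waves.

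Add previous-visit scores to the missingness regression, and describe its purpose as identifying predictors of missingness, not establishing the mechanism.

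The cost is a change of wording and slightly more analysis work. No new data are needed.

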### Cohort retention strategies

Long questionnaires and repeated follow ups may also influence attrition rates. Appropriate retention strategies will be applied to support participant retention [58]. This study will take on a multi-pronged approach in retaining participants and reducing attrition rates across the follow up timepoints. First, the outcome assessor of the participants will be kept consistent such that each participant will only be liaising with one member of the study team where a rapport has been established. Second, the questionnaire administration will adopt a barrier reducing approach in which participants will have the choice to complete the questionnaire on their own via an online digital secure form, at a time and place of their convenience or through the use of a hardcopy form. Third, through the provision of a grocery voucher after completion of the questionnaire at every timepoint, it is hoped that participants will feel incentivized to stay in the study throughout the study period.

